**Figure 3 F3:**
[figure not shown]
Automated and manual process for obtaining loyalty card purchasing data from high street retailer(s) (a) Automated process showing secure data transfer between retailer (Tesco) and the CLOCS-2 research team following participant consent. (b) Manual process illustrating participant-mediated data sharing, including data request, download and submission steps.

For both participating retailers, a barcode ID will be generated for each primary registered cardholder by the CLOCS-2 team prior to transfer from Imperial College London to the high street retailer (figure 3). We will ask participants to provide their full name (as written on the loyalty card) and loyalty card number. The CLOCS-2 team will send the CSV file that contains a unique study ID, name of the individual and the exact loyalty card number specific to the retailer using the secure file transfer. The respective high street retailers will validate the participant information from the consent form and their loyalty card data from the health questionnaire. High street retailers will then centrally generate a dataset for all consenting individuals, in accordance with data sharing agreements, and will share participants’ past purchase data with the CLOCS-2 team for the period prior to the date of recruitment.

### Data merge

The CLOCS-2 team will receive the encrypted participant purchase history from the high street retailers through the SFTP, save and store all data to a secure and encrypted server based on the CSRE at Imperial College London, described in the Data Management section. All data will be pseudonymised and analysed on the secure server.

### Data deletion

The information relating to the participants’ consents to providing past purchase data will be retained in line with each high street retailer’s data retention policy. Ten years after the study is complete, all paper-based and electronically held identifiable data including the electronic consent forms will be destroyed or deleted in accordance with Imperial College London’s data deletion and retention processes.

Contact details will be kept in REDCap at Imperial College London only for project management and facilitation purposes while the project is actively recruiting and participant data is stored on REDCap. Once the data has been fully transferred from REDCap to the CSRE, contact details will be permanently deleted unless participants have authorised us to retain them for follow-up research or to receive study results once published.

Past purchase loyalty card data and health data (as entered by participants through REDCap) will be kept pseudonymised either until all the results are published or until 5 years after the study has completed, whichever comes first. Then all past purchase data and health data will be fully anonymised and any link to identifiable data deleted.

### Sample size and statistical power

A power calculation was conducted for the following four cancers: ovarian, pancreatic, oesophageal and colorectal. This calculation was based on the former CLOCS study^19^ which was conducted using conditional logistic regression of matched pairs. The calculation assumes an effect size of OR=1.38, with 80% power at alpha=0.05 and estimates n=223 case-control pairs are needed for each cancer type. To allow for attrition of ~10%, the total number we will aim to recruit for each of these four cancers will be 250 (n=1000). No power calculation has been done for the remaining six types of cancer as these are being piloted, but the aim is to recruit 75 participants per cancer.

### Statistical methods

We will use descriptive statistics to provide details on the characteristics of cases and controls by sociodemographic (eg, age, sex and ethnicity), cancer type and by risk factors.^11^ We will report feasibility factors, including the number of participants with a loyalty card from either participating retailer, the number with cards from both retailers and the number of years of data available for analysis.

We will aim to define the time by which cases and controls become statistically significantly different in their purchase behaviours using a multivariable, conditional logistic regression model with cancer as the outcome and ‘purchase proportion’ at different timepoints to diagnosis as the exposure, adjusting for potentially confounding variables. This analysis will be repeated and stratified by cancer type, stage at diagnosis and sociodemographic factors. Analyses will be performed for different types of medications and cancers separately and combined.

We will compare proportions using Fisher’s exact tests comparing target (items suspected to be used to treat cancer symptoms) and non-target (all other items) purchases. These comparisons will be made between cases and controls at each month prior to diagnosis. For controls, the reference will be the average monthly proportions of purchases across the observation period. Target items for analysis will include, but will not be limited to, medications for pain, indigestion, bloating relief and fatigue, along with other items commonly used to alleviate cancer-related and non-specific symptoms.^11^

We will conduct exploratory analyses to establish a potential risk profile for each participant and cancer type. This will be defined as a mathematical summation of all relevant risk factors, based on the published literature.^11^ In line with the findings from the original CLOCS, this analysis will be exploratory.^19^ Furthermore, we will investigate additional methods that leverage autocorrelation in the longitudinal data. Specifically, we will examine the evolution of individual purchasing frequencies and purchase trajectories to identify patterns—such as increases in purchases prior to diagnosis or distinct purchase peaks—that may be indicative or predictive of disease onset and time to onset.

All analyses will be done using statistical software R.

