## Study objectives

The primary objective of this case-control study is to identify the time points at which participants with the following cancers (cases): oesophageal, stomach (gastric), colorectal (bowel), pancreatic, liver, bladder, endometrial, uterine sarcoma, ovarian and vulval, show statistically significant differences in their purchasing behaviours compared with purchase behaviours of participants without a cancer diagnosis (controls) over the previous 6 years. For controls, the purchases included are those recorded from participant consent to the study, up to a maximum of 6 years prior. For cases, the purchases included are those recorded up to the date of cancer diagnosis, to a maximum of 6 years, depending on when the diagnosis occurred. These behaviours include the purchase of items suspected of being used for symptom management (eg, painkillers, indigestion tablets) as well as changes in the frequency or quantity of other items purchased leading up to diagnosis. Participants’ historic loyalty card data will be collected from two major high street retailers.

The secondary objectives of CLOCS-2 are to: (1) Define a purchase threshold that may act as an “alert” for potential cancer symptoms in individuals and assess the predictive value of purchasing behaviours in the early detection of these cancers, (2) Develop a predictive model to determine the accuracy and efficacy of these purchasing behaviours for early cancer detection and (3) Create risk profiles from the participants’ self-reported health data and incorporate these into the analyses.

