### Data extraction from the high street retailers

For both high street retailers, we will request up to 6 years in total of back-dated purchase data. The exact amount of data available for each participant will depend on how long they have had their loyalty card. Following participant consent, this data will be backdated from the date of study consent for controls or from the date of cancer diagnosis for cases.

The process for requesting data will differ between the two participating high street retailers. For Tesco, we will also use their Open ID Connect platform (figure 3). To facilitate this, a custom landing page was built which directs participants from REDCap to the retailer’s OpenID platform where participants will be able to sign in using their store login details. This ensures the retailer receives direct consent from the participants to share their loyalty card data with the CLOCS-2 research team. This approach eliminates the need for manual identity verification (eg, uploading ID documents), which was a barrier in the original CLOCS. It streamlines the process, reduces participant burden and improves data security by allowing the retailer to authenticate participants directly. It also ensures compliance with the retailer policies for sharing purchase data with third parties.

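### The primary result is the time at which purchases become statistically significantly different; that time reflects chance months or sample size and does not validly estimate lead time

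*Protocol article*

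**What the plan says.** Study objectives: "The primary objective of this case-control study is to identify the time points at which participants with the following cancers", followed by all ten cancers, "show statistically significant differences in their purchasing behaviours compared with purchase behaviours of participants without a cancer diagnosis", over the previous 6 years. The criterion is significance; no size of effect is named.

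Statistical methods repeats the rule for the main model: "We will aim to define the time by which cases and controls become statistically significantly different in their purchase behaviours". That model is a conditional logistic regression with purchase proportion at several timepoints as the exposure. The number and spacing of those timepoints are not given. The next paragraph adds Fisher's exact tests of target against non-target items: "These comparisons will be made between cases and controls at each month prior to diagnosis". Data extraction sets the look-back: "we will request up to 6 years in total of back-dated purchase data".

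The regression is repeated by cancer type, stage and sociodemographic factors, and "Analyses will be performed for different types of medications and cancers separately and combined".

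Sample size and statistical power assumes one OR of 1.38 with 80% power at alpha 0.05, giving 223 pairs for each of four cancers, raised to 250 for attrition. For the others: "No power calculation has been done for the remaining six types of cancer as these are being piloted", with 75 participants each.

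**The concern.** A time defined by significance is where a test statistic crosses a line. It depends on the size of the effect, on noise and on the number of pairs. With many timepoints searched, a crossing can occur far from diagnosis by chance. If chance crossings are screened out, the crossing moves earlier as the sample grows, with behaviour unchanged.

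The lead time is the study's main product. The article lists comparison across cancer types as a strength, yet it plans 250 cases for four cancers and 75 for six, and stage and sociodemographic strata are smaller still. The primary objective also covers all ten cancers on equal terms, although the Introduction and the power section call six of them pilots without power.

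**Working it through.** **Plan's own figures.** 223/0.9 = 247.8, rounded to 250; 4 x 250 + 6 x 75 = 1450. Both agree with the article. The 223 itself cannot be confirmed, because the exposure scale and within-pair correlation are not given. For a continuous exposure with the OR per SD and no within-pair correlation, (1.960 + 0.842)^2 / [(ln 1.38)^2 / 2] = 7.849/0.0519, or 152 pairs; 223 results at a correlation of 0.32. Below, 223 pairs are taken to give 80% power for one two-sided test at 0.05.

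**False months, no true effect.** Inputs: 6 x 12 = 72 monthly Fisher tests per cancer and product; level 0.05, assumed from the power section.
- Expected number: 72 x 0.05 = 3.6, whatever the correlation.
- Independent months: 1 - 0.95^72 = 0.975.
- Simulated correlated z-tests (40,000 runs): AR(1) 0.5 gives 96%, 0.9 gives 70%, 0.95 gives 51%. Exchangeable 0.3 gives 89%, 0.5 gives 71%, 0.7 gives 45%, 0.9 gives 21%.
- If fewer timepoints are used, 12 independent tests give 46% and 6 give 26%.

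**Power against the search.** Holding 72 tests by Bonferroni (0.05/72 = 0.00069, critical value 3.392) leaves power of Phi(2.802 - 3.392) = 28% in a given month; about 510 pairs would restore 80%. Bonferroni is conservative for correlated months and is not the plan's method, so this is an upper bound on the cost.

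**Effect of sample size.** Assumed trajectory, not from the documents: a difference rising linearly from zero at month 18 to 0.5 SD at diagnosis. Mean z at month m is 0.5(1 - m/18) x sqrt(n/2). Without noise, z reaches 1.96 at m = 18[1 - 1.96/(0.5 sqrt(n/2))]:
- n = 75: 18(1 - 1.96/3.062) = 6.5
- n = 225 (250 less 10%): 18(1 - 1.96/5.303) = 11.3

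These are noise-free crossings, not expected first significant months. With noise, over 72 monthly tests (40,000 runs):

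| Reading of the rule | AR(1) | 75 pairs | 225 pairs |
|---|---|---|---|
| Mean first significant month, 0.05 | 0.5 | 50.9 | 51.2 |
| Mean first significant month, 0.05 | 0.8 | 42.1 | 42.8 |
| Mean start of unbroken run to diagnosis, 0.05 | 0.5 | 3.3 | 9.0 |
| Mean start of unbroken run to diagnosis, 0.05 | 0.8 | 4.4 | 9.9 |
| Median first significant month, Bonferroni | 0.5 | 2 | 8 |
| Median first significant month, Bonferroni | 0.8 | 1 | 7 |

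The uncorrected first significant month falls at or before the true onset in about 76-91% of runs at either n (about 60% at AR(1) 0.9). It barely depends on n because it is mostly noise. The other two readings remove most of the noise and then depend on n. A second assumed shape, with the log OR rising from month 12 through ln 1.38 at month 8, gives the same direction without noise: month 7 at n = 75, 9 at 223-250 and 11 at 2000.

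**The case against.** The strongest reply is that this is a condensed article and that error control and the form of the lag model belong in an analysis plan that is not shown. That stands for the multiplicity rule: its absence here is not the point. It does not answer the rest, because the stated objective itself makes significance the definition of the result, and the Bonferroni rows show that error control leaves the time dependent on n.

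Several stronger readings are tempting, and the documents do not support them.
- A reader might infer a fixed rule of 72 regressions at p<0.05 with the first hit reported. The monthly spacing belongs to the Fisher comparisons, the regression timepoints are not counted, 0.05 appears only in the power section, and the wording could mean a sustained difference.
- A reader might infer that a false month is almost certain. That needs weak correlation. The article acknowledges autocorrelation and reuses one control average in every monthly Fisher test, which makes the tests positively correlated. At exchangeable 0.9 the chance is 21% for one series and 1 - 0.79^4 = 61% across four independent cancers.
- A reader might infer that the power calculation describes a test of pain and indigestion purchases at 8-9 months. It names no window and no product.
- A reader might infer that the original CLOCS result goes untested or that a chance month would set the alert threshold. The scan includes those products and months, without priority, and the threshold is a separate secondary objective.

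**Conclusion.** The point holds as a fault in a stated rule. A lead time defined by statistical significance is not a valid estimate of when purchasing changes: read as the first significant month it is mostly chance, and read as a sustained or error-controlled difference it depends on sample size. In the illustration, identical behaviour gives about month 3-4 with 75 pairs and 9-10 with 225, so lead times cannot be compared between the powered and pilot cancers. The 80% power applies to one test, not to the search.

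The 3.6 expected false months rest on 72 tests at an assumed 0.05. The chance of at least one false month runs from 21% to 97.5% over the correlations examined, and the documents give none. The month figures rest on an assumed trajectory and AR(1) correlation of 0.5-0.8; the direction does not depend on that choice of shape. Severity: should-fix.

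**What to change.** 1. Replace the significance-defined time with an estimated one. Model the log OR as a smooth function of months before the index date (spline or change-point lag model within the conditional logistic framework). Report the divergence time, or the time at which a pre-specified minimum effect is reached, with a 95% CI and simultaneous bands for the curve.
2. Label the month-by-month and item scans exploratory, or control them within each cancer, for example by within-pair max-T permutation.
3. Pre-specify one confirmatory contrast for each of the four powered cancers. For ovarian cancer, where the aim is to validate CLOCS, this can be pain plus indigestion purchases in the CLOCS window. That window must be written down, since the abstract gives 8-9 months and the Introduction up to 9. For the other three, use a pre-specified window or a global test of the lag curve, because nothing in the documents supports carrying over the ovarian window. State that the 80% power applies only to such a single test.
4. Limit confirmatory claims to those four cancers and report the six pilots as estimates with intervals.

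The cost is protocol and analysis-plan wording plus modelling and permutation code, with no new participants or data. The downside is that fewer individual months can be called significant and the six pilot cancers leave the confirmatory objective.

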**Trial registration number:**

NCT06447064, CPMS58679; pre-results.

STRENGTHS AND LIMITATIONS OF THIS STUDYA key strength is the use of longitudinal purchase data recorded up to 6 years prior to enrolment, enabling analysis of temporal patterns before diagnosis.A further strength is the inclusion of multiple cancer types within a single study design, allowing comparison across groups.A key limitation is the incomplete capture of purchasing behaviour due to inconsistent loyalty card use and transactions outside participating retailers.Another limitation is the potential for exposure misclassification due to reliance on self-reported health survey data among cases and controls.

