#### GP practices

After submitting an expression of interest, new RDNs or PCNs will receive further study information and set up an organisation information document (OID) for each participating GP practice. The OID developed with the North London RDN will serve as a template for other networks. A brief site initiation visit (SIV) will be held with each new RDN/PCN conducted by the CLOCS-2 team.

Clinical team members at each GP practice will identify potential study participants with a primary diagnosis of one of the eligible cancers, received in the last 2 years prior to recruitment date. Eligible cases will be randomly selected if the number of potential participants exceeds the required size. GP practices will match invited cases with eligible controls based on age bracket, sex and the number of inhabitants. Controls will be randomly sampled from participants without a cancer diagnosis who meet the matching criteria, typically selecting one control per case. Once eligible participants are identified, the GP practice will send a text message (drafted by the CLOCS-2 team).

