### Health survey

After completing consent, participants will be required to complete an online questionnaire (approximately 50 min) about their health, medical history and lifestyle (figure 2). The design of this questionnaire has been informed by our understanding of well-established cancer risk factors and symptoms reported by patients across the target cancers in previous research.^11^ Participants with a cancer diagnosis will also be asked to provide details on the cancer type (oesophageal, stomach (gastric), colorectal (bowel), pancreatic, liver, bladder, endometrial, uterine sarcoma, ovarian and vulval) and stage (I, II, III and IV) of cancer. We will use this information to inform risk assessment and to stratify loyalty card purchasing data for cases and controls by time of diagnosis. Purchasing patterns will then be examined by cancer type and stage at diagnoses.

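### Refitting the model within strata cannot show that cancer types, stages or sociodemographic groups differ, and it drops matched pairs when the stratifying factor is not a matching factor

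*Protocol article*

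**What the plan says.** Protocol article, Statistical methods, gives the aim of the main model: "We will aim to define the time by which cases and controls become statistically significantly different in their purchase behaviours". The model is a multivariable conditional logistic regression, with cancer as outcome and purchase proportion at successive times before diagnosis as exposure. Two sentences extend it: "This analysis will be repeated and stratified by cancer type, stage at diagnosis and sociodemographic factors" and "Analyses will be performed for different types of medications and cancers separately and combined". No other method for comparing strata is described.

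The strengths and limitations box lists as a strength the "inclusion of multiple cancer types within a single study design, allowing comparison across groups". The Health survey section says: "Purchasing patterns will then be examined by cancer type and stage at diagnoses".

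Sample size and statistical power sets 223 pairs (250 recruited) for each of four cancers, at OR 1.38, 80% power and alpha 0.05. For the others it states: "No power calculation has been done for the remaining six types of cancer as these are being piloted", with a target of 75 each. The primary objective nevertheless names all ten cancers.

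Under GP practices, the matching rule is: "GP practices will match invited cases with eligible controls based on age bracket, sex and the number of inhabitants". Typically one control is selected per case. The sociodemographic examples in Statistical methods are age, sex and ethnicity. Ethnicity is not a matching factor.

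**The concern.** Each refit tests whether the OR equals 1 in that stratum. A comparison across groups needs a different null: that the OR is the same in all of them. One stratum reaching significance while another does not is weak evidence of a difference, above all when the strata differ in size by design. A time point defined by significance also depends on sample size. If the OR rises towards diagnosis, a smaller stratum will cross the significance line later, or never, on the same trajectory.

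The second problem concerns data loss. A conditional model uses within-pair contrasts. If the data are split by a factor on which case and control can differ, any pair falling across the split contributes to neither part.

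At stake is whether a cancer, stage or population group is described as having or lacking a purchase signal when the data do not separate it from the rest.

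**Working it through.** **Inputs from the documents.** OR 1.38, 80% power, alpha 0.05, 223 pairs, about 10% attrition, 250 recruited for each of four cancers and 75 for each of six. Since 4 × 250 + 6 × 75 = 1450 equals the case target, the 75 are cases, hence up to 75 pairs.

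**Assumptions.** Two-sided testing, one time point, independent strata sharing one true OR of 1.38.

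**The plan's own figure.** For an OR per SD of a continuous exposure in matched pairs, n = (1.96 + 0.842)² / [ln(1.38)² × (1 − ρ)/2]. This gives 152 pairs at within-pair correlation ρ = 0 and 223 at ρ = 0.32. The exposure scale and ρ are not stated, so 223 is attainable but not fixed by the stated inputs. Attrition: 223/0.9 = 248, consistent with 250. The steps below take 80% power at 223 pairs as given and need no value of ρ.

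**Power by stratum size.**
- SE of the log OR at 223 pairs = 0.3221/2.802 = 0.115.
- At 75 pairs, SE = 0.115 × √(223/75) = 0.198, so z = 1.62 and power is about 37%. After 10% attrition (67.5 pairs) it is about 34%.

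**How often equal effects give different results.**
- Two powered cancers: 2 × 0.8 × 0.2 = 32%.
- All four powered cancers, some significant and some not: 1 − 0.8⁴ − 0.2⁴ = 59%.
- One powered and one pilot cancer: 0.8 × 0.63 + 0.2 × 0.37 = 58%.

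A heterogeneity test across the four powered cancers, simulated with 200,000 draws under the common OR, rejected 5.0% of the time.

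**An illustration.** Suppose the observed OR is exactly 1.38 in both a powered and a pilot cancer.
- 223 pairs: 95% CI = exp(0.322 ± 0.225) = 1.10 to 1.73, p about 0.005.
- 75 pairs: 95% CI = exp(0.322 ± 0.389) = 0.94 to 2.04, p about 0.10.
- Ratio of ORs: 1.00, with SE √(0.115² + 0.198²) = 0.229 and 95% CI 0.64 to 1.57.

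The smallest observed OR that reaches significance is exp(0.225) = 1.25 in the first and exp(0.389) = 1.47 in the second.

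**Pairs lost on an unmatched binary factor.** With prevalence q and independence within pairs, 2q(1 − q) of pairs are discordant: 18% at q = 0.1, 32% at 0.2, 42% at 0.3 and 50% at 0.5. At q = 0.2 and 223 pairs:
- about 71 pairs fall in neither stratum (0.32 × 223);
- about 9 pairs have both members in the smaller stratum (0.04 × 223), although about 45 cases belong to it (0.2 × 223).

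If the factor has within-pair correlation r, the lost share is 2q(1 − q)(1 − r). At q = 0.2 and an assumed r = 0.5 this is 16%.

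Cancer type and stage belong to the case and carry the control along, and sex and age bracket are matched. Splitting on these four loses no pairs.

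**Power of the direct comparison.** For OR 1.38 versus 1.00 at 223 pairs each, SE = 0.115 × √2 = 0.163, so z = 1.98 and power is about 51%. For 80% power, the ratio of ORs must be about exp(2.802 × 0.163) = 1.58.

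**The case against.** The strongest reply is that nothing in the article says strata will be declared different because one is significant and another is not. The text speaks of repeating, stratifying and examining. A reader might infer the p-value contrast from a significance-defined result set beside a claim of comparison, but the documents do not state such a rule. The full protocol and any analysis plan are not shown and may name an interaction test, so its absence from the article is not itself a fault. All of this stands. What remains is the method that is stated: a stratified refit, which does not supply the advertised comparison and, for unmatched factors, uses less of the data than it could.

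The within-cancer test is also the question the four prioritised cancers were powered for. That stands too, and those tests should not be replaced. The planned combined analysis gives a pooled OR; it does not test whether the cancers differ.

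The 32% figure is largely stratum power restated. True, and that is the point: disagreement between significance results reflects power and says little about whether effects differ. The low power of the pilot cancers is disclosed, but the primary objective still applies the significance criterion to all ten.

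The pair loss is narrow in scope. Ethnicity appears only in the sentence on descriptive statistics, and people paired within one practice may resemble each other, which would reduce the loss. Both qualifications stand.

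**Conclusion.** The point holds as a better method for part of the stated analysis. It does not show that the primary within-cancer tests are wrong. Under a common OR of 1.38 and the plan's own 80% power, two powered cancers disagree in significance 32% of the time, and a pilot cancer detects the effect only about 37% of the time with all 75 pairs retained. These figures assume one time point, two-sided testing and independent strata. The pair loss of 32% further assumes a 20% prevalence and independence within pairs. It applies only to factors outside the matching set, and is smaller if pairs are alike.

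A reader might also infer that faulty contrasts would feed cancer-specific alert thresholds. The objectives speak of a purchase threshold without making it cancer-specific, and no section links it to contrasts between strata, so that harm is not claimed here.

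**What to change.** - Keep the tests of OR = 1 within each of the four powered cancers.
- For any statement that cancer types, stages or sociodemographic groups differ, fit one conditional logistic model on all matched pairs, with purchase-by-factor interaction terms at each time point analysed. Enter the case's type or stage as a pair-level attribute; its main effect cancels within pairs and only the product term is estimated. For an unmatched factor, enter the participant's own value and its interaction with purchase, so that discordant pairs stay in.
- Base such statements on the ratio of ORs with its CI.
- Report the six pilot cancers as ORs with CIs, and say that non-significance there is not evidence of no signal.

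The cost is wording in the analysis section and one further model per time point on data already planned, with no extra participants. The drawback is low power for interactions: about 51% for OR 1.38 versus 1.00 between two powered cancers, and less where a pilot cancer is involved. Fewer between-group claims will be made.
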